
#### Target population

Adult male and female patients with acute skin, intestinal or liver GvHD according to published criteria of the International Bone Marrow Transplant Registry and lack of response to corticosteroid treatment will be enrolled. In GvHD, a gender distribution of 2:1 (male to female) is expected. Gender or age do not impact on response and are not considered risk factors. Therefore we will not stratify for gender or age in this study. Written informed consent must be obtained from the patient before starting any study related procedures. After all screening evaluations have been performed patients meeting all inclusion and none of the exclusion criteria can be included into the study.

#### Inclusion criteria

For inclusion into the study, patients must fulfill all of the following criteria:Acute skin, intestinal or liver GvHD > grade 1 according to standard criteriaHistological confirmation in case of acute intestinal GvHDAge ≥ 18 yearsFailure of previous treatment, defined as presence of at least one of the following criteria:Treatment with prednisone/prednisolone/methylprednisolone in a dose of at least 2 mg/kg and lack of response after at least 7 days treatmentTreatment with prednisone/prednisolone /methylprednisolone in a dose of at least 2 mg/kg and progression after at least 3 days of treatmentFailure to taper the prednisone/prednisolone dose to 0.6 mg/kg/day or methylprednisolone dose to < 0.5 mg/kg/dayWritten informed consentAbility to understand the nature of the study and the study related procedures and to comply with them

#### Exclusion criteria

Patients are not eligible for this study if they fulfill one or more of the following exclusion criteria:Uncontrolled underlying diseaseActive bleedingAbsence of clinical signs of acute GvHD [23]Diagnostic or distinctive clinical signs of chronic GvHD [1]Uncontrolled bacterial, viral or fungal infectionAny previous JAK2 inhibitor treatment prior to study enrolment, except ruxolitinib given prior to the allogeneic stem cell transplantationKnown Hypersensitivity to ruxolitinib or any of the excipientsKnown positivity for HIV, Hepatitis B or Hepatitis C at the time of screening.Female patients who are pregnant or breast feedingConcomitant use of any other investigational drug within the last thirty days before the start of this study

### Study treatment

#### Ruxolitinib treatment

Ruxolitinib treatment will be administered for 6 months or as long as the patient experiences benefit from treatment with ruxolitinib. In this case treatment might be prolonged at the discretion of the investigator. In patients with CR or stable PR (≥ 4 weeks) and off steroids, ruxolitinib will be tapered. Patients randomized to ruxolitinib and BAT who do not meet the primary endpoint at day 28 will discontinue ruxolitinib and will be treated at the discretion of the investigator. In case of relapse of underlying malignancy, the study treatment will be permanently discontinued.

#### Best available treatment (BAT)

Prior to randomization, the most appropriate systemic BAT treatment will be selected as investigators choice in a patient-individualized manner based on the Onkopedia/DGHO guidelines for treatment of acute GvHD as of January 2017 [22].

### Data collection and follow-up

#### Screening assessment

The following examinations and laboratory tests will be performed at screening within 8 days and day − 1 prior to first intake of medication; physical examination, current disease status, clinical GvHD grading, standard laboratory tests, CMV PCR, QoL, evaluation of concomitant and GvHD medication. When screening assessments are completed, check and validation of inclusion and exclusion criteria for the study is performed. Detailed information on all screening evaluations is given in Additional file 1: Table S1 and Table S2.

#### Assessments during the treatment phase

Treatment visits are performed weekly from day 1 to week 6; bi-weekly from week 8 to week 12; monthly from week 16 to week 24. If the patient benefit from treatment with ruxolitinib the treatment might be prolonged at the discretion of the investigator. Therefore bi-monthly visits will be scheduled. Treatment visits contain physical examination, clinical GvHD grading, measurements of standard laboratory tests, CMV PCR, QoL, evaluation of concomitant and GvHD medication, assessment of adverse events and evaluation of number of in-hospital days. Detailed information on all assessments during the treatment phase is given in Additional file 1: Table S1 and Table S2.

#### Assessments during the follow-up phase

After end of treatment patients continue with follow up within the study. The following information will be assessed each time the patient visits the site for Follow up visit (every 2 months for 12 months): physical examination, clinical GvHD grading, standard laboratory tests, CMV PCR, QoL, evaluation of concomitant and GvHD medication, assessment of adverse events and evaluation of number of in-hospital days.

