Binary secondary endpoints (e.g. proportion of patients with CR, proportion of patients dis-continuing treatment) will be estimated as rates and presented with exact two-sided 95% confidence intervals derived from the binomial distribution. Furthermore, the same type of logistic model using treatment assignment, aGvHD grade and number of immunosuppressive treatments as covariates will be applied.

OS and EFS probabilities will be estimated and displayed using the Kaplan Meier method.

The analysis of secondary time-to-event endpoints with competing risks (e.g. time to response, response duration, time to cGvHD development) will be performed by means of the Aalen Johanson estimator for the calculation of cumulative incidence rates. Appropriate Regression models (Cox models for OS, EFS, Fine and Gray models for endpoints with competing events) will be applied. For FFS, different types of failure will be analyzed separately, considering the other types of failure and onset of cGvHD as competing events. For evaluating QOL, scores will be calculated according to the EORTC QLQ-C30 Scoring Manual [24]. The scores at screening will be summarized and for different time points during follow-up, differences of the scores to the screening scores will be calculated in FAS and the PP set.

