## Discussion

Retrospective data suggest that JAK1/2 inhibition with ruxolitinib can induce clinically meaningful and ongoing responses in heavily pretreated patients with acute and chronic steroid-refractory GvHD. To confirm these observations, single arm (NCT02953678, NCT02997280, NCT02806375) and randomized prospective trials (NCT02913261, NCT03112603) are ongoing. To establish the benefit of ruxolitinib versus best available treatment (BAT), a randomized design is needed. This trial (NCT02396628) is intended to examine ruxolitinib as add-on to BAT versus BAT alone. Thus, previously started GvHD treatments can be continued in addition to ruxolitinib at the discretion of the investigator. There is no limitation of previous and concomitant lines of aGvHD treatments, since patients in our retrospective series had a median number of three (range: 1–7) previous GvHD therapies [19]. This trial allows cross-over from BAT to BAT and ruxolitinib for patients receiving BAT not achieving the primary endpoint at day 28, with loss of response after day 28 or failure to taper steroids. However in both arms, in case of deterioration of GvHD within the first 14 days or lack of improvement, treatment may be permanently discontinued at the discretion of the investigator. In this case, the protocol recommends individual case-by-case discussion with the sponsor. Patients in the ruxolitinib arm not meeting the primary endpoint at day 28 will discontinue ruxolitinib and will be treated at the discretion of the investigator, although in our retrospective analysis we observed responses in aGvHD up to week eleven of treatment. The duration of treatment will be 6 months or as long as the patient experiences benefit from ruxolitinib treatment. In case of CR or stable PR (≥ 4 weeks) and off steroids, ruxolitinib is slowly tapered starting at day 56. In case of reappearance of GvHD signs during tapering or after tapering has been completed, the dose may be increased or treatment with ruxolitinib may be reinstituted. Hematological adverse events will be recorded but however, dose interruptions and dose reductions during treatment due to hematological adverse events are optional and as required in the investigators opinion. Also, baseline cytopenias are not prohibitive for inclusion. The protocol includes dose modifications for drug-related, non-hematological adverse events that are not GvHD related. As a unique feature of this trial, study drug is provided by regular prescription beyond approved indication. Accounting of study drug was approved by the Gemeinsame Bundesausschuss (GBA) according to § 35c Abs. 2 SGB V.

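### Follow-up is counted from end of treatment while the survival endpoints run from randomisation, so censoring after about month 13 depends on response and arm and late curves can be biased

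*Protocol article*

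**What the plan says.** **Follow-up.** Under Assessments during the follow-up phase, the Protocol article states "After end of treatment patients continue with follow up within the study". Information is collected "each time the patient visits the site for Follow up visit (every 2 months for 12 months". Planned observation from randomisation is therefore time on treatment plus 12 months.

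**Time on treatment.** Under Ruxolitinib treatment: "Ruxolitinib treatment will be administered for 6 months or as long as the patient experiences benefit from treatment with ruxolitinib". For the ruxolitinib arm the same section adds: "Patients randomized to ruxolitinib and BAT who do not meet the primary endpoint at day 28 will discontinue ruxolitinib". The Discussion states "This trial allows cross-over from BAT to BAT and ruxolitinib for patients receiving BAT not achieving the primary endpoint at day 28". It also allows treatment in either arm to be stopped for good in the first 14 days if GvHD worsens, or for lack of improvement. Prolonged treatment is described only for ruxolitinib.

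**Endpoints and methods.** Under Secondary endpoints, overall survival (OS), event-free survival (EFS), non-relapse mortality (NRM), failure-free survival (FFS), relapse, graft failure and chronic GvHD are all timed from randomisation. Under Statistical planning, "OS and EFS probabilities will be estimated and displayed using the Kaplan Meier method". Cox models are named for OS and EFS; Aalen-Johansen estimation and Fine-Gray models are named for endpoints with competing events. The article gives no common horizon for these analyses. It does set one for time to response, whose arm comparison stops at day 28.

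**The concern.** All four methods need censoring to be unrelated to prognosis, given what is in the analysis. A clock that starts when treatment stops does not secure this, because the article's own rules tie the stop date to day-28 response. Poor responders leave observation first. After they leave, the arm's curve is carried by responders, and the estimator treats their hazard as that of everyone still alive.

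The two arms are not affected equally. A ruxolitinib-arm non-responder stops ruxolitinib at day 28, while a BAT-arm non-responder may start a course of it. The mix of patients still under observation after month 13 can therefore differ between arms for reasons unrelated to the effect being estimated. OS, EFS and NRM are the secondary endpoints on which this matters most. The article reports a median OS of 18 months in its retrospective acute GvHD series, which lies inside the exposed period.

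Counts are affected more simply. Adverse events, CMV reactivation and nights in hospital are collected through follow-up and have no stated window, so raw totals cover periods of different length.

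**Working it through.** **Design figure.** The article's sample size is not in dispute. For 50% v 30%, one-sided 5%, 80% power and a χ² test without continuity correction, the calculation gives 74 per group, 148 in all, as stated; 148 × 1.08 = 159.8, hence 160. Nothing below changes it.

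**Planned observation from randomisation** (28 days = 28/30.44 = 0.92 months):

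| Patient | Treatment time + 12 months | Total |
|---|---|---|
| Ruxolitinib arm, non-responder | 0.92 + 12 | about 12.9 months |
| Ruxolitinib arm, responder | 6 + 12, or longer | 18 months or more |
| BAT arm, crosses over, 6-month course | 0.92 + 6 + 12 | about 18.9 months or more |

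The first row takes stopping ruxolitinib as end of treatment. The third takes a 6-month course after cross-over. The article states neither.

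**Ruxolitinib arm, illustration.** From the article: 50% responders (the sample-size assumption). Assumed: exponential survival, with 1-year OS of 75% in responders and 50% in non-responders. The mean is 62.5%; it was chosen to lie near the 62.4% reported for the retrospective acute GvHD series, which gives no split by response.

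- Survival in a group with 1-year OS *a*: S(t) = a^(t/12).
- True OS at 17.9 months: 0.5 × 0.75^(17.9/12) + 0.5 × 0.50^(17.9/12) = 0.5 × 0.651 + 0.5 × 0.356 = 50.3%.
- OS at 12.92 months, when non-responders are censored: 0.5 × 0.734 + 0.5 × 0.474 = 60.4%. Kaplan-Meier is correct to here.
- Afterwards only responders are at risk: Kaplan-Meier = 0.604 × 0.75^((17.9 − 12.92)/12) = 0.604 × 0.8875 = 53.6%.
- Bias: 53.6 − 50.3 = +3.3 points. At 15 months it is 57.5 − 55.9, about +1.5 points.

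**BAT arm, illustration.** From the article: 30% responders. Assumed: all non-responders cross over; half of them respond, take on the responders' hazard and complete 6 months; the other half stop at about day 56 and are censored at 1.84 + 12 = 13.84 months. The long-followed share is 0.30 + 0.35 = 0.65.

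- True OS at 17.9 months: 0.65 × 0.651 + 0.35 × 0.356 = 54.8%.
- Kaplan-Meier: (0.65 × 0.718 + 0.35 × 0.450) × 0.75^((17.9 − 13.84)/12) = 0.624 × 0.907 = 56.6%.
- Bias: +1.8 points.

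**Range at 17.9 months** (a simulation of 200,000 per arm agrees with the closed form to about 0.1 point):

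| Assumed 1-year OS, responders / non-responders | Ruxolitinib arm | BAT arm | Net shift in contrast |
|---|---|---|---|
| 75% / 50% | +3.3 | +1.8 | +1.4 |
| 75% / 35% | +3.9 | +2.2 | +1.7 |
| 80% / 25% | +3.9 | +2.1 | +1.8 |
| 62% / 62% (equal hazards) | 0 | 0 | 0 |

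Net shifts are taken from unrounded biases. In every scenario the simulated bias is zero up to month 12.9.

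**The case against.** The strongest reply has four parts.

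*The 13-month figure is an inference.* Assigned treatment is ruxolitinib plus BAT, and a non-responder who stops ruxolitinib is then treated as the investigator sees fit. The article does not say that this stop starts the follow-up clock. This stands as a condition on the finding.

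*The follow-up paragraph may not be the rule for survival status.* It lists visit assessments and does not mention vital status, relapse or graft failure. An article may leave a survival cut-off to the full protocol or analysis plan. That is fair, and no omission is charged here. What is charged is the stated anchor: followed as written, it yields response-dependent observation. An analysis plan can truncate the curves but cannot recover late data that were never collected.

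*Bias is possible, not shown.* It needs hazards that still differ by day-28 response after month 13, and curves read beyond that point. The response-specific survival figures are assumed, and the article sets no 18-month reading. This also stands.

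*The contrast moves little.* A reader might infer that BAT non-responders all stay under observation through cross-over, so that the whole 3 to 4 points fall on the comparison. The article does not support that. Cross-over is allowed, not required; the treatment duration after it is not given; nor is end of treatment for BAT-only patients. With partial response after cross-over, the BAT curve is biased in the same direction and much of the shift cancels. With 80 per arm, the standard error of an 18-month survival difference is about √(0.50 × 0.50/80 + 0.55 × 0.45/80) = 7.9 points even without censoring, well above a net shift of 1 to 2 points.

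**Conclusion.** The point holds in a limited form. The follow-up rule as stated makes length of observation depend on response and arm, provided that stopping ruxolitinib is end of treatment. Analyses timed from randomisation then have censoring after about month 13 that can be informative.

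Under the assumed survival values, OS at 18 months is overstated by about 3 to 4 points in the ruxolitinib arm. The BAT arm is overstated by about 2 points if half of crossed-over patients respond, leaving about 1 to 2 points in the contrast. All of this is zero if hazards no longer differ by response. NRM, relapse, graft failure, FFS components and chronic GvHD are exposed to the same mechanism, but no size was calculated for them. The unequal periods for unwindowed counts need no assumption about hazards.

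It would be too strong to say that the late curves *are* biased, or that the BAT arm is free of the problem. The primary endpoint, sample size, time to response and estimates to about month 12 are unaffected. This should be corrected, but it does not threaten the trial's main conclusion.

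**What to change.** Either of two changes is enough.

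1. **In the follow-up section:** follow vital status, relapse, graft failure and chronic GvHD to one common time from randomisation for every patient, whatever the treatment stop date. Cost: a few extra status contacts for patients who stop early.
2. **In the analysis section:** limit arm comparisons of OS, EFS, NRM, FFS, relapse, graft failure, chronic GvHD and event counts to 12 months from randomisation, when every patient is still due to be under observation, and treat later data as descriptive. Cost: late data drop out of the formal comparison.

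Each takes about one sentence. Neither changes the sample size, the primary analysis or any treatment rule. It would also help to state what counts as end of treatment in each arm and after cross-over, since the length of observation depends on it.

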#### Statistical planning

The sample size calculation is based on the primary endpoint response (ORR). An expected proportion of 30% for the patients with best available treatment and an expected alternative proportion of 50% for the patients with acute GvHD treated with ruxolitinib is assumed. As there is currently no satisfactory active treatment available for patients with steroid-refractory GvHD, the alternative assumption is based on published data of 60 patients with acute and chronic GvHD treated with ruxolitinib [17, 19] and on recent papers for BAT [3–5]. The study is planned to detect a response difference between treatment arms at a one-sided significance level α = 5% with a power of 1-β = 80%, when the response probabilities are 50% (ruxolitinib) and 30% (BAT). Based on the χ2 Test, 148 patients (74 per group) need to be included in the analysis. A small number of drop-outs not evaluable for the intention-to-treat analysis of the primary endpoint may occur. Further missing response will be evaluated as non-response according to the intention-to-treat principle. This might blur the assumed difference between treatment groups. Therefore we increased the calculated sample size by 8%, and 160 patients will be randomized.

The primary analysis will be based on the full analysis set (FAS) and will be conducted with a logistic regression model of the primary endpoint response to GvHD treatment as defined above. The model will include treatment assignment (ruxolitinib and BAT vs BAT only) and the stratification variables aGvHD grade (≤ grade 3 versus grade 4) and number of previous immunosuppressive treatments (≤ 3 versus ≥4) as covariates, and the primary hypothesis will be tested at a one sided level α = 5% within this model. Odds ratios will be calculated with two-sided 90% confidence intervals (CI), and the null hypothesis will be rejected in favour of the alternative, if the lower bound of the CI for the odds ratio of ruxolitinib and BAT compared to BAT only is above 1. Patients with missing response evaluation will be counted as non-responders. This analysis will be repeated in the per protocol (PP) population as a sensitivity analysis. Additionally, two-sided 95% CI will be reported in order to provide comparability with data from literature.

Binary secondary endpoints (e.g. proportion of patients with CR, proportion of patients dis-continuing treatment) will be estimated as rates and presented with exact two-sided 95% confidence intervals derived from the binomial distribution. Furthermore, the same type of logistic model using treatment assignment, aGvHD grade and number of immunosuppressive treatments as covariates will be applied.

OS and EFS probabilities will be estimated and displayed using the Kaplan Meier method.

The analysis of secondary time-to-event endpoints with competing risks (e.g. time to response, response duration, time to cGvHD development) will be performed by means of the Aalen Johanson estimator for the calculation of cumulative incidence rates. Appropriate Regression models (Cox models for OS, EFS, Fine and Gray models for endpoints with competing events) will be applied. For FFS, different types of failure will be analyzed separately, considering the other types of failure and onset of cGvHD as competing events. For evaluating QOL, scores will be calculated according to the EORTC QLQ-C30 Scoring Manual [24]. The scores at screening will be summarized and for different time points during follow-up, differences of the scores to the screening scores will be calculated in FAS and the PP set.

#### Data safety monitoring board (DSMB)

A Data Safety Monitoring Board (DSMB) is established to supervise the conduct of the trial and will be responsible for recommendations for early termination, modifications or continuation of the trial, if necessary.

## Discussion

Retrospective data suggest that JAK1/2 inhibition with ruxolitinib can induce clinically meaningful and ongoing responses in heavily pretreated patients with acute and chronic steroid-refractory GvHD. To confirm these observations, single arm (NCT02953678, NCT02997280, NCT02806375) and randomized prospective trials (NCT02913261, NCT03112603) are ongoing. To establish the benefit of ruxolitinib versus best available treatment (BAT), a randomized design is needed. This trial (NCT02396628) is intended to examine ruxolitinib as add-on to BAT versus BAT alone. Thus, previously started GvHD treatments can be continued in addition to ruxolitinib at the discretion of the investigator. There is no limitation of previous and concomitant lines of aGvHD treatments, since patients in our retrospective series had a median number of three (range: 1–7) previous GvHD therapies [19]. This trial allows cross-over from BAT to BAT and ruxolitinib for patients receiving BAT not achieving the primary endpoint at day 28, with loss of response after day 28 or failure to taper steroids. However in both arms, in case of deterioration of GvHD within the first 14 days or lack of improvement, treatment may be permanently discontinued at the discretion of the investigator. In this case, the protocol recommends individual case-by-case discussion with the sponsor. Patients in the ruxolitinib arm not meeting the primary endpoint at day 28 will discontinue ruxolitinib and will be treated at the discretion of the investigator, although in our retrospective analysis we observed responses in aGvHD up to week eleven of treatment. The duration of treatment will be 6 months or as long as the patient experiences benefit from ruxolitinib treatment. In case of CR or stable PR (≥ 4 weeks) and off steroids, ruxolitinib is slowly tapered starting at day 56. In case of reappearance of GvHD signs during tapering or after tapering has been completed, the dose may be increased or treatment with ruxolitinib may be reinstituted. Hematological adverse events will be recorded but however, dose interruptions and dose reductions during treatment due to hematological adverse events are optional and as required in the investigators opinion. Also, baseline cytopenias are not prohibitive for inclusion. The protocol includes dose modifications for drug-related, non-hematological adverse events that are not GvHD related. As a unique feature of this trial, study drug is provided by regular prescription beyond approved indication. Accounting of study drug was approved by the Gemeinsame Bundesausschuss (GBA) according to § 35c Abs. 2 SGB V.
